# Qizhu Yuling prescription in the prevention of postoperative metastasis and recurrence of esophagus cancer: study protocol for a randomized, double-blind, placebo-controlled, multicenter clinical trial

**DOI:** 10.3389/fonc.2025.1478390

**Published:** 2025-03-26

**Keywords:** Qizhu Yuling prescription, esophageal cancer, traditional Chinese medicine, randomized controlled trial, disease-free survival, protocol

## Abstract

**Background:**

Esophageal cancer (EC) is a malignant tumor with a high recurrence and metastasis rate and poor prognosis. In 2024, China ranked first in the world in terms of new EC cases and deaths. Surgery is the main treatment method for EC, but the clinical difficulty is how to prevent recurrence and metastasis after surgery. Traditional Chinese medicine as a complementary therapy has played an important role in this regard. Preclinical studies have confirmed that Qizhu Yuling Prescription (QZYLP) has anticancer effects, reduces treatment side effects, and improves quality of life, except for the lack of long-term prognostic results. Therefore, this study aims to investigate whether QZYLP can reduce the recurrence and metastasis rates of EC after surgery, improve disease-free survival (DFS), prolong overall survival, and observe the safety of the drug.

**Methods:**

This study is a multicenter, randomized, double-blind, placebo-controlled clinical trial. It seeks to enroll 310 patients from 10 hospitals who have completed adjuvant therapy following R0 surgery for esophageal squamous cell carcinoma without recurrent metastasis. Using a center-randomized design, participants will be assigned to the control group (n=155, receiving placebo treatment) or experimental group (n=155, receiving QZYLP granules treatment). Treatment will last for 6 months, with follow-up every 3 months after the final treatment or endpoint event, continuing for up to 3 years postoperatively. The primary outcome measured is DFS at 1 year postoperatively. Secondary outcomes included indicators related to prognosis, fat distribution, peripheral blood inflammation, tumor markers, and quality of life scales.

**Discussion:**

This study aims to further clarify the efficacy and safety of QZYLP in preventing postoperative recurrence and metastasis of EC, and to explore the mechanism of action. The results of this study will provide high-quality evidence for the participation of TCM in the comprehensive treatment program of EC, and improve the precise diagnosis and treatment system of TCM in EC.

**Clinical trial registration:**

ClinicalTrials.gov, identifier NCT05626309.

## Introduction

1

Esophageal cancer (EC) is one of the deadliest cancers globally. According to the Global Cancer Statistics 2022, the number of new EC cases worldwide is 511,054, ranking fourth among digestive system cancers (eleventh among all malignancies). The number of deaths was 445,391, ranking fifth among digestive system cancers (seventh among all malignancies). China ranked first in the world in terms of new EC cases and deaths, accounting for 43.8% of new cases and 42.1% of deaths (1). Chinese age-standardized incidence rate and mortality rate of EC were 8.32/10^5^ (5.0/10^5^ worldwide) and 6.68/10^5^ (4.3/10^5^ worldwide) in 2022 respectively (2). EC is a highly aggressive malignant tumor with a poor overall prognosis. In China, the surgical resection rate for EC currently ranges from 58%~92% (3). In the management of operable esophageal adenocarcinoma and certain squamous cell carcinoma cases, the established treatment paradigm incorporates induction therapy (chemotherapy with or without radiation), surgery, and postoperative adjuvant therapy. However, the total recurrence rate after radical resection is as high as 27–52.4% (4), significantly influencing patient prognosis. The *2023 NCCN Clinical Practice Guidelines in Oncology* (5) emphasize that the main focus of EC and esophagogastric tumor treatment is the management of recurrence and metastasis. Currently, the strategies to prevent recurrence and metastasis of EC after operation mainly include radiotherapy, chemotherapy, and immunotherapy. However, these treatments often face challenges such as drug resistance and toxic side effects (6–8). Moreover, the recurrence and metastasis rates are much higher during the window period after adjuvant therapy (4). Therefore, exploring new treatment strategies in this window period is crucial as standard treatments remain insufficient (9).

Throughout thousands of years of development, Traditional Chinese Medicine (TCM) has consistently been used to emphasize and advocate for preventive treatment. Increasing evidence indicates that TCM can effectively mitigate the recurrence and metastasis of malignancies (10, 11). A recent national multicenter prospective cohort study has demonstrated that the integration of TCM in the treatment of patients with post-operative stage II-IIIA non-small cell lung cancer (NSCLC) is associated with a reduction in recurrence rates by approximately 39% (12). Furthermore, a meta-analysis of randomized controlled trials has confirmed the efficacy and safety of compound kushen injection for adults with esophageal cancer (13). The Department of Oncology, Guang’anmen Hospital, China Academy of Chinese Medical Sciences (CACMS), has long been dedicated to the treatment of EC. Based on clinical experience, they have developed a Chinese herbal compound formula known as Qizhu Yuling Prescription (QZYLP). The formula consists of *Astragali Radix, Codonopsis Radix, Rhizoma Atractylodis Macrocephalae, Rhizome Curcumae, Clematidis Radix et Rhizoma, Stalactite*, and Chinese Sage Herb. This compound formula has been declared an invention patent in the People’s Republic of China, with Application No. 202210873081.0. A previous study employed QZYLP to intervene in patients with EC after postoperative radiotherapy and chemotherapy, including 55 prospective cases and 123 retrospective cases. The results showed that the median Disease-free Survival (DFS) was 43 and 31 months, respectively (14), which were both prolonged compared with similar periods in modern medical studies (15). Furthermore, the study demonstrated that QZYLP can alleviate symptoms such as fatigue, shortness of breath, and dysphagia, and it can improve quality of life, with no serious adverse effects observed. Through thorough preliminary research, QZYLP was found to exhibit anticancer effects, reduce treatment side effects, and enhance quality of life. However, there is a lack of national multicentre evidence-based support for the long-term efficacy of QZYLP in post-EC patients.

Therefore, this study aims to investigate the long-term efficacy and safety of QZYLP for preventing recurrent metastasis in postoperative EC through a large-scale, multicenter, high-quality, randomized controlled trial (RCT).

## Materials and methods

2

### Study design

2.1

This study is a multicenter, randomized, double-blind, placebo, parallel-controlled clinical trial conducted according to the protocol approved by the Medical Ethics Committee of Guang’anmen Hospital (2022-200-KY-01). It was registered with Clinical Trials (https://clinicaltrials.gov/) under the number NCT05626309. A randomized design is implemented using a centralized randomization system to conceal protocol allocation. The control group receives a placebo, while the experimental group is treated with QZYLP granules. Both groups also undergo conventional symptomatic therapy. Treatment duration spans 6 months, with follow-up continuing for 3 years post-surgery. After completing the final treatment or reaching the endpoint event, all patients entered a post-treatment follow-up period with evaluation every 3 months. The primary endpoint is the 1-year DFS rate after surgery, which is used to measure the proportion of patients who do not experience recurrence, metastasis, or death (from any cause) within 1 year following surgery. **Figure 1** shows the timeline for enrollment, intervention, and evaluation, while **Figure 2** shows the timeline for intervention and follow-up. **Table 1** depicts the study flowchart.

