### Inclusion criteria

2.3

EC without esophagogastric junction pT_1-4a_N_+_M_0_ (stage IIB-IVA) that met the diagnostic criteria without recurrence or distant metastasis;Patients who completed adjuvant therapy (including adjuvant radiotherapy, chemotherapy, chemotherapy + radiotherapy) within 6 months after R0 resection for EC.ECOG score 0–2.18–75 years old.Expected survival ≥ 3 months.Participants who voluntarily signed informed consent.

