### Sample size calculation

2.9

This study is a RCT. The test group was administered QZYLP Granules, while the control group was placed on a placebo. The primary outcome measure was the postoperative DFS of patients. The study was designed as a superiority trial with a 1:1 ratio between the test and control groups. According to the literature, the mDFS for patients with lymph node-positive esophageal squamous carcinoma after surgery with adjuvant therapy is 19.3 months (19). Assuming that the DFS of the test group was 12 months longer than that of the control group, with α=0.05 and 1-β=0.80, the expected time to enroll all participants was 24 months, and the total duration of the clinical trial was expected to be 36 months, with a consistent enrollment rate of the study participants. Using PASS 11 software, it was calculated that 140 cases were needed in each of the test and control groups. Considering a 10% dropout rate, 155 participants were enrolled in the test and control groups, resulting in a final number of 310 participants. The following formula was used (20). Here δ=π_1_-π_2_.

$$n={\left(\frac{u_{\alpha }+u_{\beta }}{\delta }\right)}^{2}[\pi_{1}(1-\pi_{1})+\pi_{2}(1-\pi_{2})]$$

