### Interventions

2.10

The experimental group was administered QZYLP granules. Patients were administered two small packets in the morning and two small packets in the evening. The medication was dissolved in hot water before administration. Each course of treatment lasted 4 weeks, with six courses in total. The patients will be followed up for up to 3 years after their EC surgery.

The control group was administered a placebo. The placebo was designed to be identical to the experimental drug in terms of the outer packaging, color, shape, and taste. It was prepared from maltodextrin and food coloring. The raw materials of maltodextrin conformed to the relevant provisions of excipients - maltodextrin in the *Chinese Pharmacopoeia 2015 edition, Part Four* (21). The food coloring included caramel coloring, egg yolk coloring, and milk chocolate brown pigment, all of which were edible-grade ingredients. The dosing method was comparable to that of the experimental group.

During the experimental treatment, drugs for managing myelosuppression, nausea and vomiting, diarrhea, abnormal liver and kidney functions, infections, and other symptomatic treatments were allowed concurrently. However, the specific symptoms and the combined use of these drugs were accurately recorded. The following were prohibited: (1) Other antitumor therapies (including chemotherapy, immunotherapy, molecular targeted therapy, and radiotherapy) (2) Chinese herbal decoctions, Chinese herbal injections, and Chinese patent medicine with antitumor effects.

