#### Primary outcome

2.11.1

1-year DFS rate: Refers to the proportion of patients who did not experience recurrence, metastasis, or death (from any cause) within 1 year following surgery. Although OS is the gold standard for evaluating malignant tumor treatment, given the strong correlation between DFS and OS and to control of time costs, the 1-year DFS rate was selected as the primary endpoint to explore long-term efficacy (22).

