#### Secondary outcomes

2.11.2

(1) Prognosis-related indicators:

DFS: Time from randomization to tumor progression or death (from any cause).Overall survival (OS): Time from randomization to death (from any cause).Cumulative annual recurrence and metastasis rate for 1–3 years: Proportion of patients experiencing recurrence and metastasis from the day of surgery to 1, 2, and 3 years.Cumulative annual survival rate for 1–3 years: Proportion of patients surviving from the day of surgery to 1, 2, and 3 years.

(2) Indexes associated with fat distribution:

Total, Visceral, and Subcutaneous Fat Areas: These measure fat areas on cross-sectional images obtained through plain CT scanning.Visceral Adiposity Index: A new assessment of visceral fat based on waist circumference (WC), body mass index (BMI), triglyceride (TG), high-density lipoprotein (HDL), and visceral adiposity index (VAI). Male VAI = during [WC/(39.68 + 1.88 × BMI)] × (TG/1.03) × (1.31/HDL). Female VAI = during [WC/(36.58 + 1.89 × BMI)] × (TG/0.81) × (1.52/HDL).

(3) Tumor markers: squamous cell carcinoma antigen (SCC), carcinoembryonic antigen (CEA), carbohydrate antigen 19-9 CA199), and cytokeratin-19-fragment (CYFR21-1).(4) Peripheral blood inflammatory index: lymphocyte-to-monocyte ratio (LMR); lymphocyte-to-neutrophil ratio (LNR).(5) Prognostic nutritional index: Serum albumin level (g/L) + 5 × total number of peripheral blood lymphocytes (×10^9/L).(6) Symptoms and quality of life evaluation:

Quality of life of the patient: This score was assessed using the Quality of Life Questionnaire Esophageal-Specific Module 18(QLQ-QES18). Each of the 18 questions is scored from 1 to 4, with a total score ranging from 18 to 72. A higher score indicates poorer quality of life.Evaluation of the symptoms of the patients: This score was measured using the M. D. Anderson Symptom Traditional Chinese Medicine (MDASI-TCM). Each of the 26 questions was rated on a scale from 0 to 10, resulting in a total score ranging from 0 to 260. A higher score indicated more severe symptoms.

(7) Medication compliance: The number of cases and percentages were calculated for <80, 80–120, and >120% compliance.(8) Percentage of Participants with Adverse Events: Percentage of participants experiencing adverse events in different study arms.

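### The primary 1-year DFS rate is counted from surgery although patients are randomised only after adjuvant therapy, so event-free time before randomisation dilutes the treatment difference

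*Protocol article*

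**What the plan says.** Section 2.1 (Study design) of the protocol article sets the time origin: "The primary endpoint is the 1-year DFS rate after surgery". Section 2.11.1 (Primary outcome) repeats it: "Refers to the proportion of patients who did not experience recurrence, metastasis, or death (from any cause) within 1 year following surgery". The abstract agrees.

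Section 2.3 (Inclusion criteria) admits "Patients who completed adjuvant therapy (including adjuvant radiotherapy, chemotherapy, chemotherapy + radiotherapy) within 6 months after R0 resection for EC", and the cancer must be one "that met the diagnostic criteria without recurrence or distant metastasis". The Discussion, where it lists the strengths of the design, places the start of the intervention at the end of adjuvant therapy. Section 2.10 (Interventions) gives the length of treatment: "Each course of treatment lasted 4 weeks, with six courses in total", that is 24 weeks.

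Section 2.11.2 (Secondary outcomes) uses a different origin: "DFS: Time from randomization to tumor progression or death (from any cause"). Overall survival is also timed from randomisation.

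Section 2.9 (Sample size calculation) works from a control median DFS that "after surgery with adjuvant therapy is 19.3 months" and a 12-month gain in the test arm. It assumes 24 months of accrual, 36 months in total, 80% power and 140 per arm before dropout.

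**The concern.** A patient who relapses or dies between surgery and the end of adjuvant therapy never enters the trial. Every randomised patient has therefore already passed part of the primary year without an event, and did so before receiving any study drug. Those months add successes to both arms and no information on treatment.

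The remaining window also differs between patients. Someone randomised at month 3 has 9 months in which the primary event can occur. Someone randomised at month 6 has 6 months, about the length of the six courses, so almost no post-treatment time enters the primary endpoint. Yet section 2.11.1 chose this endpoint to explore long-term efficacy.

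At stake are the size and the meaning of the primary result. Both 1-year rates will look better than the prognosis of these patients from entry, and the absolute difference will understate what the drug does over a year.

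**Working it through.** **Inputs.** Control median 19.3 months, test median 19.3 + 12 = 31.3 months, 140 per arm, accrual 24 months and total 36 months (all section 2.9); two-sided 0.05 (section 2.14). Assumptions of this check: exponential survival, both medians applied from randomisation, and a single entry time *r* (months after surgery) for all patients. The article gives no distribution of *r*; months 3 and 6 are shown as a range, with 6 the limit for completing adjuvant therapy.

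**Step 1: the plan's own figure.** Hazards are ln2/19.3 = 0.03591 and ln2/31.3 = 0.02215 per month, a hazard ratio of 0.617. Schoenfeld events: 4(1.96 + 0.8416)²/(ln 0.617)² = 134.3, so 135. With uniform accrual, the event probability in an arm is 1 − [exp(−12λ) − exp(−36λ)]/(24λ), giving 0.564 and 0.405. Patients per arm: 134.3/(0.564 + 0.405) = 138.5, so 139. This reproduces the stated 140 as a two-sided log-rank design, with about 80% power for DFS as a time-to-event outcome.

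**Step 2: the 1-year rate with each clock.** Time at risk within the primary year is w = 12 − r. The rates are exp(−0.03591w) and exp(−0.02215w). With *d* their difference and *v* the sum of p(1 − p) over the two arms, power = Φ(d/√(v/140) − 1.96).

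| Clock | w (months) | Control | Test | Difference | d/√(v/140) | Power |
|---|---|---|---|---|---|---|
| Randomisation | 12 | 65.0% | 76.7% | 11.7 points | 0.1168/0.0539 = 2.167 | 58% |
| Surgery, r = 3 | 9 | 72.4% | 81.9% | 9.5 points | 0.0955/0.0499 = 1.915 | 48% |
| Surgery, r = 6 | 6 | 80.6% | 87.6% | 6.9 points | 0.0694/0.0435 = 1.595 | 36% |

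A pooled-variance version gives 58%, 48% and 35% at 140 per arm, and 62%, 52% and 39% at 155 per arm.

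**Step 3: what the clock costs.** The surgery clock keeps 9.5/11.7 = 82% of the difference at r = 3 and 6.9/11.7 = 59% at r = 6, a loss of about 18% to 41%. By the pooled formula, 80% power would need 237 per arm with the clock at randomisation, 303 at r = 3 and 435 at r = 6.

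**Step 4: separating two losses.** The fall from 80% to 58% comes from testing a 1-year proportion with a sample size built for a log-rank test, and would occur with either clock. Only the fall from 58% to 48% (r = 3) or to 36% (r = 6) belongs to the surgery origin.

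**The case against.** The strongest reply is that nothing here is biased. Randomisation and blinding make the pre-randomisation time alike in both arms, type I error is intact, and the hazard ratio after randomisation is untouched. That is right: the cost is in sensitivity and interpretation.

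A second reply is that the loss depends on guessed entry times and a constant hazard. The Introduction says that recurrence is much more frequent in the period after adjuvant therapy. If the hazard were 1.5 times as high for the first 6 months after entry, with the same hazard ratio, entry at month 6 would give 1.5 × 6 = 9 month-equivalents, hence 72.4% vs 81.9% and 9.5 points. The dependence is real, but the comparison moves too. Over 12 months from randomisation the same patients would have 9 + 6 = 15 month-equivalents: exp(−0.03591 × 15) = 58.4% vs exp(−0.02215 × 15) = 71.7%, a difference of 13.4 points before rounding. The surgery clock still loses 1 − 9.5/13.4 = 29%.

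A third reply is that two origins need not be a contradiction. Yearly rates are anchored at surgery throughout, and the DFS timed from randomisation is a separately named outcome. This is fair. The problem is which origin the primary uses. The difference between tumour progression and recurrence or metastasis is mostly wording in patients who were resected and disease-free at entry.

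A reader might also infer that late entrants have little or no primary window, since the 6-month limit concerns completion of adjuvant therapy and the article states no maximum time to randomisation. The documents do not support this. Sections 2.3 and 3 together point to entry at about month 6 or earlier, which leaves about half the year, and a limit may stand in the full protocol, which is not shown.

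**Conclusion.** The point holds as a loss of sensitivity and clarity in the primary endpoint. Because eligibility requires patients to be recurrence-free after adjuvant therapy, the surgery clock counts event-free time in which the drug cannot act. On the plan's own medians, the expected difference falls from 11.7 points to between 9.5 and 6.9, and power from 58% to between 48% and 36%, for entry at months 3 to 6.

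These figures rest on exponential survival, an effect that begins at randomisation, assumed entry times, and the 19.3-month median applied from randomisation, although the article describes it as a figure after surgery with adjuvant therapy.

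Two stronger readings should be avoided. The finding does not show a biased comparison. Nor does it explain the whole gap between the stated 80% and the power of the 1-year rate: the step from 80% to 58% has another cause.

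**What to change.** Before unblinding, define the primary 1-year DFS rate as the Kaplan-Meier estimate at 12 months from randomisation. Use one event definition (recurrence, metastasis or death from any cause) for both the primary and the secondary DFS, with the same origin as section 2.11.2 already sets. Report surgery-anchored rates descriptively.

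Do not attach the stated 80% power to the 1-year rate. After re-anchoring it is about 58% at 140 per arm and 62% at 155, and 237 per arm would be needed for 80%. That mismatch between endpoint and sample size has to be settled separately.

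The cost is an amendment to the registered primary outcome while the trial is running (recruitment began in October 2022), and less direct comparison with literature that counts from surgery. The last patient must be followed for 12 months from randomisation; the planned 24 months of accrual within 36 months already provides for this, though the extension of recruitment noted under Trial status moves the calendar date.

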**Figure 1 f1:**
[figure not shown]
Study flow chart.

**Figure 2 f2:**
[figure not shown]
Intervention and follow-up flow chart.

**Table 1 T1:** Flowchart of treatment phases.

Project		Lead-in period	Intervention period				Follow-up period
Timepoint		1	End of the first course of treatment	End of the second course of treatment	End of the third course of treatment	End of the N course of treatment	N+X
Week		-W1-W0	W4-W5	W8-W9	W12-W13	W4N-W4N+1	Every 3 months
Inclusion/exclusion criteria		✓					
Informed consent		✓					
Medical history							
Demographic data		✓					
Diagnosis		✓					
Therapeutic observation							
Vital signs		✓	✓	✓	✓	✓	
Clinical examination		✓	✓	✓	✓	✓	✓
Physical condition score		✓	✓	✓	✓	✓	✓
Clinical symptoms		✓	✓	✓	✓	✓	
Description of tongue and pulse		✓	✓	✓	✓	✓	
TCM syndrome		✓	✓	✓	✓	✓	
Imaging Examination	PET-CT/CT	✓			✓	✓	✓
	MRI、B-ultrasound	*			*	*	*
	Bone scanning	*			*	*	*
	Gastroscope	*			*		*
Tumor marker		✓	✓	✓	✓	✓	✓
Indexes related to fat distribution		✓	✓	✓	✓	✓	✓
MDASI-TCM		✓	✓	✓	✓	✓	
QLQ-QES18		✓	✓	✓	✓	✓	
Safety observation							
Routine blood tests		✓	✓	✓	✓	✓	✓
Liver/kidney function		✓	✓	✓	✓	✓	✓
Routine urine/stool tests		*	*	*	*	*	*
ECG		✓	✓	✓	✓	✓	✓
CTCAE			✓	✓	✓	✓	
Other work							
Drug combination			✓	✓	✓	✓	
Efficacy evaluation			✓	✓	✓	✓	✓
Treatment							✓

**Table 1** The schedule of participants. *Indicates: This examination is optional. For imaging examinations, the same examination method should be used for screening of the same site and for each review after enrollment, and the examination should be reviewed every 3 sessions during the treatment phase and every 3 months during the follow-up phase. Head, chest, and abdominal examinations should be selected as appropriate. If CT/MRI examination has been done for the same site, abdominal X-ray examination and ultrasound examination are not necessary. Bone scanning examination is selected according to the patient’s condition. TCM, Traditional Chinese Medicine. PET-CT, Positron Emission Tomography Computed Tomography. CT, Computed Tomography. ECG, Electrocardiogram. MRI, Magnetic Resonance Imaging. MDASI-TCM, M.D.Anderson Symptom Traditional Chinese Medicine. QLQ-QES18, Quality of Life Questionnaire of Oesophageal-Specific Module 18. CTCAE, Common Terminology Criteria for Adverse Events. ✓ Indicates: This work needs to be performed.

